#### Data collection

There is insufficient evidence to support the cost-benefit ratio of screening asymptomatic individuals. Nonetheless, this study’s testing plan follows the 2020 recommendations of the Fleischner Society [1]. Details of data that will be collected during the scheme are described in the Online Supplementary Materials (Supplementary Table 1).

Patients will be enrolled after confirming that they fulfil all inclusion criteria without meeting any exclusion criteria and they provide informed signed consent. In addition, the following data will be collected and registered at enrolment: (i) sex, date of birth, height, weight, and BMI; (ii) reason for a referral from screening facilities; (iii) smoking history, environmental history (presence or absence of dust exposure, contact with birds, and occupational history), and family history of interstitial pneumonia; (iv) comorbidities, including diabetes mellitus, coronary artery disease, gastroesophageal reflux, cardiovascular diseases other than coronary artery disease, and lung cancer; and (v) presence of fine crackles on auscultation, chest radiography, and HRCT findings and patterns based on international guidelines [7].

The following physical examination results will be collected every six months: oxygen saturation (SpO_2_) levels and dyspnoea scale score (modified Medical Research Council), pulmonary function tests, blood gas analysis, and a 6-min walk test. Other tests with results include biological assessments (including blood count and renal and hepatic functions), autoantibody screening blood sampling, serum interstitial pneumonia markers (Krebs von den Lungen-6 (KL-6), surfactant protein-D (SP-D)), ILD-GAP index, and echocardiography results. Suspected diagnosis and diagnostic accuracy of IPF based on ontology will be recorded after discussing the multidisciplinary diagnosis (MDD) via a web conference involving the three institutions and each institution’s diagnosis.

Patients that show any signs of disease progression, including the appearance of clinical symptoms, decline in lung function, or exacerbation of HRCT findings evaluated by visual assessment and AIQCT [13], will be considered for a full work-up and the introduction of drug therapy. The detailed examination will include bronchoalveolar lavage (BAL), transbronchial lung cryobiopsy, or surgical lung biopsy. After registration, subsequent pulmonary complications requiring hospitalisation, such as acute exacerbation, pneumonia, pneumothorax, or lung cancer, will be recorded.

Furthermore, it will be recorded if long-term oxygen therapy is needed in cases of progression despite appropriate medication during the follow-up years. When therapeutic intervention is introduced, the assessment plan is reset, and regular assessments are carried out during the period from the introduction of treatment (Supplementary Table 2).

#### Management of enrolled participants

Data and images obtained during routine observation will be shared with the three medical centres via electronic data capture (EDC) and the imaging cloud. Based on the data, each of the three medical centres performs a case-specific institutional MDD and registers it in the EDC. HRCT images will also be evaluated independently by two experienced chest radiologists ([name] and [name]) for the first 100 cases at the start of enrolment to check the concordance rate of HRCT findings. Starting from the 101st case after the concordance rate is confirmed, each one will be assessed by one radiologist. Cases in which cryobiopsy or surgical lung biopsy is performed are referred to a pulmonary pathologist for pathological diagnosis, and the results are recorded on the EDC. In addition, cases registered at the three screening medical centres are regularly web-case-conferenced between facilities. Furthermore, the facility MDD and the web-conference MDD will be recorded on the EDC.

#### Timing of the start of treatment

Regular mandatory check-ups are carried out every six months by a registered researcher at a medical screening centre and progression is assessed according to the Progressive Fibrosing-Interstitial Lung Disease progression criteria [15]. If deemed to be a progression, the facility MDD will also be consulted and a decision will be made to introduce therapeutic agents.

### Statistical analysis

#### Sample size calculation

There are ≥ 70,000 examinees yearly for the Japanese Red Cross Kumamoto Hospital Health Care Center and the Center for Preventive Medicine of Saiseikai Kumamoto Hospital. The number of participants suspected of having ILAs was approximately 300 at each centre in 2018. Therefore, the total number of participants with ILAs is assumed to be approximately 600 per year.

According to the previous data, the number of cases will be underestimated by 10% because approximately 10% of the medical check-ups that require detailed tests for ILAs did not undergo the subsequent detailed examinations. Therefore, the maximum number of suspected ILAs is expected to be 500 cases annually.

Continuous variables will be expressed as means and standard deviation (SD), or medians and interquartile ranges (IQRs), and categorical variables for each group will be expressed as the number of subjects and percentages. The inter-observer variation in the presence or absence of HRCT findings will be analysed using the weighted kappa statistic and classified as follows: poor (κ = 0–0.20), fair (κ = 0.21–0.40), moderate (κ = 0.41–0.60), substantial (κ = 0.61–0.80), and almost perfect (κ = 0.81–1.00). Inter-observer variation regarding the extent of the HRCT findings was assessed using Spearman’s rank correlation coefficient. The HRCT scores assigned by the two independent observers are compared using the Bland–Altman method. If the HRCT patterns or scores do not agree between the two radiologists; one of the patterns or scores is adopted by consensus.

All analyses with ILA progression as the outcome variable are performed using logistic regression, where ILA progression was dichotomised with progression defined as probable or definite progression, and regression defined as no change, probable regression, and definite regression using subjective visual estimation as well as an objective AIQCT. Multivariable analyses will be adjusted for variables such as age, sex, and smoking status. In addition, a Cox proportional-hazards model has been created to assess treatment efficacy, considering the immortal period as a time-dependent covariate.

Furthermore, morbidity and mortality related to respiratory disease will be compared between groups using chi-squared or Fisher’s exact tests. Finally, variation in the global extent of ILA on HRCT examination between each evaluation timepoint will be compared between groups using the Mann–Whitney U or Wilcoxon tests. The extent of ILA according to a visual semi-quantified score or a quantified score by AI will be assessed by the Wilcoxon test for trends over time per case. The degree of progression for each diagnosed group of IPF or PPF will be compared with these scores using the Mann–Whitney U test.

Clinical laboratory evaluations will be expressed as mean, median, and interquartile range for each evaluation timepoint, and boxplots will be created for graphical representation. In addition, percentages of abnormal clinical laboratory results will be compared between the groups using chi-squared or Fisher’s exact tests. No interim data analysis has been planned.

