### Relationship between AI analysis for quantification of ILA on HRCT scans and clinical outcomes

AI and machine learning approaches have become increasingly important for quantifying and classifying ILA and fibrotic ILDs [13]. They will also help address the increasing demand for identifying the progression of ILA. In this study, quantitative assessments of ILA using AI will be combined with visual assessments that semi-quantify the visual extent of ILA in 5% increments, as well as the pattern of HRCT findings in line with the 2022 IPF international guidelines [7]. The presence or absence of progression will be assessed quantitatively using AI (AIQCT) and semi-quantitatively by visual assessment. The relationship between the degree of progression and HRCT pattern at enrolment and changes in lung function indices and serum markers will also be investigated.

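### Reader agreement on HRCT extent is summarised by Spearman's correlation, which measures association and cannot show a systematic difference between the two radiologists (minor; Bland–Altman is also planned)

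*Protocol article*

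**What the plan says.** The relevant text follows the sample size paragraphs under Statistical analysis. It treats reader agreement in three parts.

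- Presence or absence of findings: "The inter-observer variation in the presence or absence of HRCT findings will be analysed using the weighted kappa statistic", with five descriptive bands for kappa.
- Extent: "Inter-observer variation regarding the extent of the HRCT findings was assessed using Spearman", completed by the words for the rank correlation coefficient.
- Scores: "The HRCT scores assigned by the two independent observers are compared using the Bland–Altman method".

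Where the two radiologists differ on a pattern or score, "one of the patterns or scores is adopted by consensus".

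Management of enrolled participants describes the double reading. Two chest radiologists read independently "for the first 100 cases at the start of enrolment to check the concordance rate of HRCT findings". Then: "Starting from the 101st case after the concordance rate is confirmed, each one will be assessed by one radiologist". That section names no statistic and no limit for the check.

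The Discussion section on AI analysis gives the scale. Visual assessment will "semi-quantify the visual extent of ILA in 5% increments".

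**The concern.** Agreement asks whether two readers give the same value. Rank correlation asks whether they order the cases alike. A reader who is consistently more generous, by a fixed amount or by a fixed factor, keeps the order intact, so Spearman's coefficient does not move. Yet a consistent difference between readers is a main thing that a double-reading exercise should find.

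Extent scores are used later. The statistical section tests them for trend over time within each case and compares the degree of progression between the IPF and PPF groups. One step on the scale is also the smallest change that the visual score can record. From case 101 there is no second reader to correct a difference. With at most 500 participants a year for 3 years, up to 1,500 − 100 = 1,400 cases would be single-read. A summary coefficient that looks excellent whether or not the readers differ systematically is a poor basis for describing the quality of those scores.

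**Working it through.** The article reports no agreement coefficient, acceptance limit or score distribution, so there is no figure of its own to reproduce. The check is of how the named statistic behaves.

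**Inputs.** From the article: 100 double-read cases and a 5-point scoring step. Assumed, because the article gives no spread of scores: reader A scores (i) uniformly from 5% to 30% in 5-point steps, (ii) uniformly from 5% to 50%, or (iii) with mean 12.5% and SD 8.1%. Reader B scores A + 5 (one step higher) or 2A (twofold).

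**Spearman.** The coefficient uses ranks only. A + 5 and 2A are strictly increasing in A, so the ranks of A and B are identical and the coefficient is 1.00. This needs no assumption about the spread. Exact agreement is 0 of 100 in both situations.

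**Absolute agreement.** With mean m and SD s for reader A, the concordance coefficient (close to the absolute-agreement single-reader ICC at n = 100) is:

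- for B = A + c: 2s² / (2s² + c²)
- for B = kA: 2ks² / [(1 + k²)s² + (k − 1)²m²]

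For spread (iii), s² = 65.61 and m² = 156.25:

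- A + 5: 131.22 / (131.22 + 25) = 0.84
- 2A: 262.44 / (328.05 + 156.25) = 0.54

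**Bland–Altman.** The bias is the mean of B − A, and the 95% limits are bias ± 1.96 × SD of B − A. For B = 2A the difference equals A. Under (iii) this gives 12.5 ± 1.96 × 8.1, or −3.4 to 28.4.

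Results for (i) and (ii) come from simulated sets of 100 cases, those for (iii) from the formulas.

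| Spread of A | Reader B | Spearman | ICC | Bland–Altman bias (95% limits) |
|---|---|---|---|---|
| (i) 5–30% | A + 5 | 1.00 | 0.85 | +5.0 |
| (i) 5–30% | 2A | 1.00 | 0.43 | +17.6 (0.8 to 34.3) |
| (ii) 5–50% | A + 5 | 1.00 | 0.94 | +5.0 |
| (ii) 5–50% | 2A | 1.00 | 0.44 | +29.1 (1.0 to 57.2) |
| (iii) mean 12.5%, SD 8.1% | A + 5 | 1.00 | 0.84 | +5.0 |
| (iii) mean 12.5%, SD 8.1% | 2A | 1.00 | 0.54 | +12.5 (−3.4 to 28.4) |

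Under a pure shift the limits coincide with the bias. Under doubling the difference also rises with the mean score, with slope 1/1.5 = 0.67, which the plot would show.

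**With reading noise.** Let reader B also err by one step in 30% of cases (assumed). Spearman is then 0.97 for spread (i) and 0.98 for (ii), and is unchanged when the shift or the doubling is added. On the same data Bland–Altman moves from a bias near zero (−0.05 and −0.55) to +4.95 and +4.45 with the shift.

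Two things follow. Spearman does not register the bias at all, and Bland–Altman does. An ICC falls heavily for doubling but only to about 0.84 to 0.94 for a one-step shift.

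**The case against.** The strongest reply is that the plan already contains the right tool. Bland–Altman comes in the very next sentence and shows both kinds of bias directly, and disagreements among double-read cases are settled by consensus. This stands, and it is why the point is minor. It does not turn Spearman into a measure of agreement, and consensus works only while there are two readers.

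A second reply is that an ICC would hardly flag a one-step shift. That also stands, and so the ICC should not be used alone.

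Three stronger readings may tempt a reader, and the document supports none of them.

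- That single reading from case 101 depends on Spearman. The article ties it to a concordance rate for HRCT findings and names no statistic. Kappa or the Bland–Altman result fits at least as well. The acceptance rule may stand in the full protocol or analysis plan, so its absence here is no fault.
- That reader bias shifts the 5% threshold for ILA. Under Inclusion criteria, ILA is diagnosed by pulmonologists and confirmed in institutional conferences. A radiologist's concordance is one optional support. The primary endpoint is likewise a diagnosis of IPF or PPF, with diagnoses reached by multidisciplinary discussion, and not an extent score.
- That serial change is distorted. This requires one patient's scans to go to different readers, which the article does not say. With one reader per patient a constant shift cancels in within-patient change. Progression is also assessed by AI-based quantitative CT, which does not depend on the radiologist.

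Finally, a noise-free doubling between two experienced chest radiologists is an extreme illustration and not a forecast.

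**Conclusion.** The point holds in a narrow form. The coefficient named for inter-observer variation in extent measures association and not agreement. It stays at 1.00 under any constant upward or downward shift and any proportional difference between readers. That result is mathematical and rests on no assumption. The ICC and Bland–Altman figures do rest on assumed score distributions, and the noisy results on an assumed error rate. They illustrate and do not predict.

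Because Bland–Altman is planned on the same scores, a systematic difference need not go unseen. What remains is that the headline coefficient for extent could be reported as good agreement beside a one-step bias. Nothing in the article links this to the primary endpoint. Severity: minor.

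**What to change.** In the statistical section, replace Spearman's coefficient for extent with a two-way, absolute-agreement, single-reader ICC with a 95% CI. Quadratic-weighted kappa on the 5% categories, also with a 95% CI, is an acceptable alternative. Keep the Bland–Altman comparison.

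State that extent concordance in the first 100 cases is judged on the ICC together with the Bland–Altman bias and limits, and not on the ICC alone, since it may still look acceptable under a one-step shift.

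This is an edit of a sentence or two. It uses the same 100 double reads and the same two readers. The one downside is that the reported agreement figure may be less favourable than a rank correlation.

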### Participant characteristics

#### Study population

Eligible candidates are not only cases with suspected ILA on chest CT at health check-up facilities, but also cases confirmed by the health check-up facilities to have reticular shadows at the costophrenic angles on chest X-ray with or without the presence of fine crackles on auscultation, assuming no history of interstitial pneumonia. Training sessions will be held for physicians in the screening check-up facilities participating in the study to confirm the study participants using any of these three findings. Cases with either of these findings in the screening check-up facilities are suspected cases of ILA. The study will enrol approximately 500 patients from > 70,000 examinees in general health check-up facilities, annually screened by chest radiography, with fine crackles on auscultation and/or CT findings. Participants will be enrolled over 3 years and followed up for 5 years. The primary outcome is the evaluation of the aetiological data of preclinical patients who are subsequently diagnosed with IPF or PPF. This study has been designed according to the Strengthening the Reporting of Observational Studies in Epidemiology Statement guidelines. Patients or the public were involved in the design, conduct, reporting, or dissemination plans of our research.

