#### Exclusion criteria

The following are exclusion criteria: (i) patients who refuse to participate in the study after reading the explanation, (ii) patients with acute or subacute progressive interstitial pneumonia, (iii) patients who have difficulties undergoing the periodic follow-up due to their distant places of residence, (iv) cases that are assessed as inappropriate for the study by medical attendants, (v) cases incorporated into intervention studies, such as clinical trials that are not allowed to participate in observational studies.

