### Data collection and management

#### Primary endpoint

The primary endpoint is the frequency of subsequent IPF or PPF diagnoses.

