### Study limitations

First, since almost all patients suspected to have ILAs are asymptomatic, they may not necessarily visit a teaching hospital after referrals. For example, previous data from one of the check-up facilities (The Center for Preventive Medicine of Saiseikai Kumamoto Hospital) shows that the rate of missing re-evaluation was approximately 10%. Second, patients may fail to attend the regular 6-month visits after consenting to participate in the study because they are asymptomatic. Finally, a viral infection pandemic, such as COVID-19 or flu, might also affect regular visits every 6 months. For example, during the COVID-19 pandemic, patients feared the infection and tended to withhold regular hospital visits.

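### ILA-progression analyses are fixed as logistic regression with no time point, and the primary frequency has no rule beyond number and percentage, although missed visits are expected over 5 years

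*Protocol article*

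**What the plan says.** Primary endpoint section: "The primary endpoint is the frequency of subsequent IPF or PPF diagnoses". It gives no horizon, starting point, denominator or estimator.

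Statistical methods appear under Sample size calculation. The general descriptive rule is that "categorical variables for each group will be expressed as the number of subjects and percentages". For progression on HRCT, "All analyses with ILA progression as the outcome variable are performed using logistic regression, where ILA progression was dichotomised"; no assessment time is named, and nothing is said about incomplete follow-up. The one time-to-event method has another purpose: "a Cox proportional-hazards model has been created to assess treatment efficacy, considering the immortal period as a time-dependent covariate".

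Follow-up is 5 years with six-monthly assessments (Abstract, Study population). Study limitations says that "patients may fail to attend the regular 6-month visits after consenting to participate in the study because they are asymptomatic" and adds that a pandemic may affect attendance.

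At entry, candidates have no history of interstitial pneumonia and no earlier clinical suspicion of interstitial lung disease. The only exclusion based on lung disease is "patients with acute or subacute progressive interstitial pneumonia".

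Two wordings also conflict or mislead. Study population states that "The primary outcome is the evaluation of the aetiological data of preclinical patients who are subsequently diagnosed with IPF or PPF", which is not the quantity named under Primary endpoint. The complement of progression is labelled "regression defined as no change, probable regression, and definite regression", so stable scans are filed as regression.

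**The concern.** How often ILA becomes IPF or PPF, and which baseline features predict progression, are questions about events over time. A yes/no outcome with no time point needs everyone to be observed for the same period. If some participants stop attending, the analyst must either keep them as non-progressors or drop them. The first choice pulls the percentage down and the second pushes it up. The text does not say which applies. If attendance also differs by a baseline feature, that feature can look like a predictor when it is not. The Discussion names prognostic markers of ILA progression as an aim, so this matters.

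A related gap is that no rule separates IPF recognised at the entry work-up from IPF that develops later.

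**Working it through.** **The plan's own figure.** The article states no precision, power or expected frequency for the primary endpoint, so there is nothing to reproduce. What follows is illustrative.

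**Inputs.**
- 5-year risk of 24.4%: the Discussion's 10 of 41 people with ILA later diagnosed with interstitial lung disease after more than 4 years. It is a stand-in, because it covers any such disease and not only IPF or PPF.
- Annual loss d of 5%, 10% or 20%: assumed. The only 10% in the article is non-attendance before enrolment.
- Constant hazards, loss unrelated to outcome, no deaths: assumed.

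**Crude versus completers.**
- Event hazard λ = −ln(1 − 0.244)/5 = 0.0559 per year.
- Loss hazard θ = −ln(1 − d).
- Crude proportion = λ/(λ+θ) × (1 − e^(−5(λ+θ))).
- Events plus completers = crude/(crude + e^(−5(λ+θ))).

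For d = 10%, θ = 0.1054, λ+θ = 0.1613 and e^(−0.8065) = 0.446. Crude = 0.347 × 0.554 = 0.192. Events plus completers = 0.192/(0.192 + 0.446) = 0.301.

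| Annual loss (assumed) | True risk | Crude | Events plus completers |
|---|---|---|---|
| 5% | 24.4% | 21.6% | 27.0% |
| 10% | 24.4% | 19.2% | 30.1% |
| 20% | 24.4% | 15.1% | 37.8% |

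A discrete model on ten six-monthly visits gives similar values: 21.9% and 27.3% at 5% loss, 19.7% and 30.6% at 10%.

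**Deaths.** With no loss and an assumed 2% deaths per year, the crude percentage and the competing-risk incidence are both 23.4%. Death alone does not separate them.

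**Effect on a predictor.** Take a binary feature with no true effect whose two levels lose 5% and 15% per year (assumed; six-monthly model, 24.4% risk).
- Lost participants kept as non-progressors: 21.9% versus 17.7%. Odds ratio = (0.177/0.823)/(0.219/0.781) = 0.77. With an assumed 750 per group (half of 3 × 500), the chance of p < 0.05 is about one half (0.535).
- Lost participants dropped: 27.3% versus 34.6%. Odds ratio = (0.346/0.654)/(0.273/0.727) = 1.41.

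The sign of the spurious association depends on a coding choice that the text does not make.

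**Disease present at entry.** If a share p already had IPF and were counted, the figure becomes p + (1 − p) × 0.244. For assumed p of 2%, 5% and 10% this is 25.9%, 28.2% and 32.0%, an excess of 1.5, 3.8 and 7.6 points.

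**Together.** With 10% loss, 2% deaths and 5% present at entry, the six-monthly model gives a crude 0.05 + 0.95 × 0.190 = 23.0% against a competing-risk incidence of 23.4%. The errors can nearly cancel, so the net direction is unknown.

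**The case against.** Much of the case on the other side stands.

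- The logistic-regression sentence governs HRCT progression, listed under Further endpoints. A reader might infer that it biases the headline result, but it does not govern the primary endpoint.
- No passage states that the primary frequency will be a crude percentage. The article condenses a fuller protocol, and the estimator may be fixed there. A crude percentage is the natural reading of the only rule given, but it remains an inference.
- A reader might infer that deaths before diagnosis bias the result. They do not where death is a competing event. They matter only if the dead are dropped or treated as censored.
- A reader might infer that IPF present at entry will be counted. The word subsequent and the entry conditions show the opposite intent. What is lacking is an operational rule.
- The limitation describes missed visits, not a rate of permanent dropout. All loss rates above are assumed.
- Progression categories need a follow-up scan, so someone with none cannot be classified. This does not settle the status of someone scanned early and then lost.
- Age and smoking are planned adjustment variables. That limits confounding of other predictors through them, but the coefficients of age and smoking would still absorb any attendance difference.
- Censoring is not a complete cure. The article links absence to having no symptoms. In the extreme case where only people who would never progress leave, at 10% per year, the crude figure is exactly right at 24.4%, while a censoring estimator gives about 30%. This objection changes the remedy.
- HRCT is not among the six-monthly tests named under Data collection, so a six-monthly progression model may not be possible.

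**Conclusion.** The point holds in limited form. The firm part is that the article fixes a time-free binary model for every ILA-progression analysis, reserves time-to-event modelling for treatment efficacy, and itself expects missed visits. Progression associations are therefore open to bias from unequal follow-up. For the primary frequency the point is conditional: the same bias arises if a crude percentage is used, and no other rule is given.

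The size cannot be taken from the documents. Under the assumed 24.4% risk and 10% annual loss, one cohort could report about 19% or about 30%, depending only on how lost participants are handled. Without loss, the crude 5-year percentage is sound. The documents do not support a claim that the reported frequency will be too high, or too low, overall. The two wording conflicts are real but editorial.

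**What to change.** **Primary estimate.** State it as the 5-year cumulative incidence of a first multidisciplinary diagnosis of IPF or PPF, counted from enrolment. Treat death as a competing event, censor losses at the last assessment and give a 95% CI. Add a sensitivity analysis for informative loss, for example one that assumes lost participants did not progress. Include only participants whose enrolment multidisciplinary diagnosis is not IPF or PPF, and report the others separately as prevalent.

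**Progression models.** Replace the logistic models with a discrete-time or interval-censored model that follows the actual HRCT schedule, including baseline predictors of attendance.

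**Wording only.** Align the primary outcome under Study population with the Primary endpoint section, and call the complement of progression no progression.

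**Cost.** Mostly protocol and analysis-plan text plus some extra analysis work. The at-risk set becomes slightly smaller, and the main estimate relies on a censoring assumption, which the sensitivity analysis is there to test. Two things need confirming first: the HRCT timing in the supplementary schedule, which is not shown, and that deaths are recorded for all enrolled participants, since the article mentions mortality for IPF cases and respiratory mortality without saying so.

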## Discussion

This is the first prospective, multicentre, observational study to clarify (i) the aetiological data of patients with ILA from a large general health check-up population, (ii) the natural course of IPF or PPF from the asymptomatic stage, (iii) the effects and outcomes of early therapeutic intervention including anti-fibrotic agents for progressive cases of ILA, (iv) the new prognostic markers of ILA progression which are critical to better determine patients at a higher risk of IPF and PPF, and (v) the effectiveness of newer therapies for IPF on earlier ILA identification where therapeutic attenuation of functional decline will be more impactful than at the latter end stages of established IPF.

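### Every model of ILA progression is a yes/no logistic regression with stable scans labelled as regression, so no covariate-adjusted analysis uses the degree of progression that the study measures

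*Protocol article*

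**What the plan says.** The model is fixed in the Statistical analysis section, under Sample size calculation: "All analyses with ILA progression as the outcome variable are performed using logistic regression". The outcome is then cut in two: "ILA progression was dichotomised with progression defined as probable or definite progression, and regression defined as no change, probable regression, and definite regression". The cut applies to both ways of reading the scans, "using subjective visual estimation as well as an objective AIQCT". Multivariable analyses are adjusted for variables such as age, sex and smoking status.

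Finer scales are available. The Discussion subsection on AI analysis plans "visual assessments that semi-quantify the visual extent of ILA in 5% increments", alongside a quantitative AIQCT measure. The closing paragraphs of the statistical section use these scores uncut: "The extent of ILA according to a visual semi-quantified score or a quantified score by AI will be assessed by the Wilcoxon test", with Mann–Whitney comparisons between groups, including the IPF and PPF groups. These are rank tests without covariates.

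The Discussion lists among the study's aims "the new prognostic markers of ILA progression which are critical to better determine patients at a higher risk of IPF and PPF". The AI subsection also intends to relate the degree of progression to HRCT pattern at enrolment and to changes in lung function and serum markers.

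**The concern.** There are two separate problems.

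**Label.** A scan that has not changed has not regressed. An odds ratio reported as progression versus regression would in practice be largely a contrast with stable disease if, as is likely, most non-progressors are stable. Readers would misread it whatever the power.

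**Mismatch with the aims.** The article wants markers of progression and wants to study its degree. The only adjusted models it specifies for progression treat definite and probable progression as the same outcome. For AIQCT they reduce a quantity to yes or no. A marker that separates fast from slow progressors has no adjusted analysis in which it could show. The Background names age, smoking history, BMI and genotype as predictors of progression, so an unadjusted rank test is a weak substitute when a new marker is judged.

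**Working it through.** The article gives no alpha, power, effect size or predictor prevalence for these analyses, so there is no figure of its own to reproduce. What follows shows what the cut costs under stated assumptions.

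**Inputs from the article.** Progression rates: 20% at 2 years and above 40% at 5 years (subsection on specific MDD); 73% and 76% in two earlier cohorts (subsection on aetiological data). Enrolment: up to 500 a year for 3 years, so at most 3 × 500 = 1,500.

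**Assumptions.** Two-sided 5% test. For AIQCT: change roughly normal, and a predictor that shifts it uniformly by d standard deviations.

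**Step 1. Information kept when a normal change is cut at progression rate p.** RE = φ(z_p)² / [p(1 − p)]. At p = 0.20: 0.280² / 0.16 = 0.49.

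**Step 2. Power if the uncut analysis had 80%.** Power = Φ((1.96 + 0.8416) × √RE − 1.96).

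| p | RE | Power after the cut | Loss (points) |
|---|---|---|---|
| 0.20 | 0.490 | 50.0% | 30.0 |
| 0.40 | 0.622 | 59.8% | 20.2 |
| 0.73 | 0.555 | 55.0% | 25.0 |
| 0.76 | 0.530 | 53.2% | 26.8 |

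Equivalently, the binary model needs 1/0.622 = 1.6 to 1/0.490 = 2.0 times as many participants.

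**Step 3. Power at given numbers.** With predictor prevalence π, power = Φ(d × √(N π(1 − π) RE) − 1.96), and RE = 1 for the uncut analysis. With N = 1,500 and π = 0.5:

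| d | Uncut | Cut, p = 0.20 | Cut, p = 0.40 | Cut, p = 0.73 |
|---|---|---|---|---|
| 0.10 | 49.1% | 27.3% | 33.3% | 30.2% |
| 0.15 | 82.8% | 52.9% | 63.0% | 58.1% |
| 0.20 | 97.2% | 77.4% | 86.3% | 82.2% |
| 0.30 | 100% | 98.2% | 99.6% | 99.1% |
| 0.40 | 100% | 100% | 100% | 100% |

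So the loss is about 30 points at worst (d near 0.15), under 2 points at d = 0.3 and nil from d = 0.4. Simulation agrees: at N = 1,500, d = 0.15 and 20% progression, power is 83% continuous and 53% binary.

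Fewer participants or a rarer marker bring the loss back at d = 0.3 (progression 20% to 40%):

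- N = 500, π = 0.5: 92% uncut against 65% to 75% cut.
- N = 750, π = 0.3: 96% against 75% to 84%.
- N = 1,500, π = 0.1: 94% against 68% to 79%.

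**Step 4. Five-level visual grade.** Under proportional odds, RE = [1 − p³ − (1 − p)³] / [1 − Σp_k³]. The split over grades is not given, so it is assumed. Two examples, ordered from definite progression to definite regression:

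- 10/10/70/7/3%: RE = (1 − 0.008 − 0.512) / (1 − 0.345) = 0.480/0.655 = 0.73, so 80% power falls to 67%.
- 20/20/57/2/1%: RE = (1 − 0.064 − 0.216) / (1 − 0.201) = 0.720/0.799 = 0.90, so 80% falls to 76%.

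Over a wider set of splits (30% to 70% of progressors definite, 60% to 95% of non-progressors stable), RE runs from about 0.55 to 0.91 and the loss from about 4 to 25 points.

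**Step 5. When the grade result reverses.** Suppose a predictor changes only whether a patient progresses, not the grade among progressors or non-progressors. Simulation: N = 1,500, 30% prevalent predictor, progressors split evenly, non-progressors 87.5/8.75/3.75. Power of the five-grade rank test against the yes/no test is about 69% against 80% (20% progression in the unexposed), 75% against 81% (40%) and 58% against 79% (73%). Here the binary model is the better one by 6 to 21 points.

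**The case against.** The strongest reply is that yes/no progression is a question the article itself asks. Further endpoints names a progression rate, and the AI subsection states "The presence or absence of progression will be assessed quantitatively using AI (AIQCT) and semi-quantitatively by visual assessment". The earlier cohorts report progression as a proportion. A logistic model answers that question directly; a mean AIQCT change or a common odds ratio answers another. This stands, and it is why the logistic model should be kept at equal rank.

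A reader might infer that the cut costs this study a fixed 4 to 30 points of power. The article does not support that. The range needs an uncut analysis with 80% power, a normal AIQCT change and an assumed grade split, none of which it states. Steps 3 and 5 show that the loss can be close to nil and, for the grade, can change sign. The near-nil result is itself a favourable case: 1,500 is a ceiling, and the yearly 500 is described as a maximum of suspected cases, before HRCT confirmation and missed visits.

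A reader might also infer that the plan discards the quantitative scores altogether. It does not: they are analysed uncut over time and between groups. The gap is confined to covariate-adjusted analysis. Covariate detail can be left to a full analysis plan, but the article does not leave the model open here: it prescribes logistic regression for all analyses with progression as the outcome.

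Finally, progression is neither the primary nor a secondary endpoint; it is listed under Further endpoints. That limits the weight of the point but does not remove it.

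**Conclusion.** The point holds in a limited form. The article fixes a binary model for all progression outcomes and misnames its reference class. It specifies no adjusted analysis that uses the degree of progression, although its Discussion sets out to find progression markers and to study degree. The naming error rests on no assumption.

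For AIQCT, the cut keeps about 49% to 62% of the information at the cited progression rates if change is roughly normal and shifts uniformly. What that costs in power depends on the effect, the numbers and how common the marker is. For the visual grade, neither the size nor the direction of the loss is established. The frequency of IPF or PPF diagnosis, which is the primary endpoint, is untouched. This is a worthwhile improvement to the marker analyses, not a threat to the study's main result.

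**What to change.** In the paragraph of the statistical section that specifies logistic regression:

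- **Add an adjusted AIQCT model.** Linear regression of change in AIQCT extent (transformed or robust if skewed), adjusted for age, sex, smoking status and baseline extent.
- **Add an adjusted model for the visual grade.** Proportional-odds regression on all five levels with age, sex and smoking status, and partial proportional odds if proportionality fails.
- **Keep the yes/no logistic model alongside these**, for the progression-rate question and for comparison with earlier cohorts. Limit the sentence that now covers all progression analyses to this model.
- **Rename its reference class** to no progression (no change or regression).

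The cost is some wording, a little programming, a proportionality check and effect measures that clinicians know less well than a yes/no rate. No further scans, readers or participants are needed.
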